## Abstract

**Background:**

Suicide remains a leading cause of death among veterans in the United States, and mild traumatic brain injury (mTBI) increases the risk of suicidal ideation (SI) and suicide attempts (SAs). mTBI worsens impulsivity and contributes to poor social and occupational functioning, which further increases the risk of SI and SAs. Repetitive transcranial magnetic stimulation is a neuromodulatory treatment approach that induces neuroplasticity, potentially repairing neurodamage. Intermittent theta burst stimulation (iTBS) is a second-generation form of transcranial magnetic stimulation that is safe, shorter in duration, displays a minimal side effect profile and is a promising treatment approach for impulsivity in mTBI. Our novel proposed treatment protocol uses frontal pole iTBS to target the ventromedial prefrontal cortex, which may reduce impulsivity by strengthening functional connectivity between the limbic system and frontal cortex, allowing for improved top-down control of impulsive reactions, including SI and SAs.

**Objective:**

The objectives of this study are to (1) develop an iTBS intervention for veterans with mTBI, impulsivity, and SI; (2) assess the feasibility and tolerability of the intervention; and (3) gather preliminary clinical outcome data on SI, impulsivity, and functions that will guide future studies.

**Methods:**

This is a pilot, double-blinded, randomized controlled trial. In developing this protocol, we referenced the SPIRIT (Standard Protocol Items: Recommendations for Interventional Trials) guidelines. We will enroll 56 participants (28 active iTBS and 28 sham iTBS). The iTBS intervention will be performed daily, 5 days a week, for 2 weeks. We will collect 10 validated, psychometric, quantitative outcome measures before, during, and after the intervention. Measures included will assess functioning, impulsivity, suicidality, posttraumatic stress disorder, and depressive symptoms. We will collect qualitative data through semistructured interviews to elicit feedback on the participants’ experiences and symptoms. We will perform quantitative and qualitative analyses to (1) assess the feasibility, tolerability, and acceptability of the treatment; (2) gather advanced neuroimaging data to assess neural changes elicited by treatment; and (3) assess improvements in outcome measures of impulsivity and suicidality in veterans with mTBI.

**Results:**

This study protocol was approved by the Edward Hines, Jr. VA Hospital Institutional Review Board (Hines IRB number 14-003). This novel treatment is a 5-year research project (April 1, 2023, to March 31, 2028) funded by the Veterans Administration Rehabilitation Research and Development service (CDA2 award IK2 RX002938). Study results will be disseminated at or before the project’s end date in March 2028.

**Conclusions:**

We will provide preliminary evidence of the safety, feasibility, and acceptability of a novel frontal pole iTBS treatment for mTBI, impulsivity, SI and SAs, and functional deficits.

**Trial Registration:**

ClinicalTrials.gov NCT05647044; https://clinicaltrials.gov/study/NCT05647044

**International Registered Report Identifier (IRRID):**

PRR1-10.2196/58206

## Introduction

### Background

The prevalence of suicide among veterans who served in the US military is devastatingly high. Veterans die by suicide at almost double the rate of civilians in the United States [1]. The prevalence of suicide among veterans with traumatic brain injury (TBI) is even higher. Veterans with TBI are 1.5 times more likely to die by suicide than veterans without TBI, even when controlling for comorbid psychiatric conditions [1,2]. These statistics are particularly concerning given that there have been >400,000 new TBI diagnoses among US service members since the beginning of operations Enduring Freedom, Iraqi Freedom, and New Dawn, of which >80% are mild traumatic brain injury (mTBI) [3]. Overall, between 16% and 20% of all operations Enduring Freedom, Iraqi Freedom, and New Dawn veterans have a history of mTBI, and among them, up to 22% report suicidal ideation (SI) [4].

TBI consists of any external force applied to the head of any individual, resulting in vascular and axonal damage, edema, and neuronal death [5]. TBI is clinically further subcategorized by the severity of the injury as either mild, moderate, or severe. mTBI is defined as a loss of consciousness for <30 minutes, postconcussive altered mental status or amnesia for <24 hours, a Glasgow Coma Score, following injury of 13 to 15 (15 being the maximum score), and lack of abnormalities on standard clinical magnetic resonance imaging (MRI) or computed tomography [6]. TBI is an extremely common injury, resulting in an estimated 4.8 million independent emergency room visits throughout the United States annually [7-9]. TBI results in a significant economic burden: the cost of nonfatal TBI amounts to >US $40 billion per year in the United States [10]. Globally, TBI resulted in the loss of 246.7 million disability-adjusted life years between 1990 and 2013 [11].

Given the high suicide rate among US veterans, suicide prevention is a high-priority issue for the US Veterans Administration (VA) [12]. The US VA has assembled task forces that have created clinical practice guidelines for the assessment and management of veterans at risk for suicide [13]. These guidelines establish substantial risk factors to help providers identify which veterans are at the highest risk. The guidelines specifically cite having a history of TBI, functional deficits, past SI, and a history of impulsivity as independent risk factors for developing SI [13]. TBI predisposes individuals to functional deficits [14,15] and impulsivity [16], and those with impulsivity likely struggle with functional deficits [17]. Given these findings, we hypothesize that these conditions may be interrelated and could serve as meaningful behavioral targets in the treatment of SI.

Transcranial magnetic stimulation (TMS) therapy was first described by Barker et al [18]. Seminal studies by George et al [19] demonstrated the efficacy of TMS in the treatment of depression in large, multisite sham-controlled trials. TMS was subsequently approved by the US Food and Drug Administration (FDA) in 2008 for the treatment of major depressive disorder [20]. TMS was first hypothesized as a treatment for TBI by Pape et al [21]. It was later shown to be effective in treating several TBI sequelae, including depression [22]. TMS also has demonstrated efficacy in the treatment of posttraumatic stress disorder (PTSD), chronic pain, cognitive deficits, and headaches in individuals with mTBI [23-27]. A second-generation form of TMS, intermittent theta burst stimulation (iTBS), was first shown to treat depression in 2009 in a study by Holzer and Padberg [28]. In a large, noninferiority study comparing iTBS and TMS, patients with treatment-resistant depression show similar safety and adverse event (AE) profiles and exhibit improvements in their depressive symptoms to both interventions [29].

This study aims to create a novel iTBS intervention to reduce impulsivity and SI among veterans with mTBI while improving overall social and occupational functioning. This study will be conducted at the Edward Hines, Jr. VA Hospital in Hines, Illinois. We are interested in stimulating the ventromedial prefrontal cortex (VMPFC) with iTBS because the VMPFC appears to exhibit less functional connectivity with the limbic system in individuals with mTBI [30]. This diminished connectivity is suspected to be responsible for impulsivity and SI in individuals with mTBI [30-32]. To the best of our knowledge, no established treatment approach has used VMPFC iTBS to improve social and occupational functioning, SI, and negative urgency impulsivity among individuals with mTBI and comorbid mental illness. A list of the common terms used in the study and their definitions are provided in Textbox 1.

Terms and definitions used in the study.Mild traumatic brain injury: a type of brain injury resulting from mechanical forces defined by loss of consciousness for <30 minutes, Glasgow Coma Score of 13-15, post-concussive altered mental status or amnesia <24 hours, and normal findings on neuroimagingNegative urgency impulsivity: a form of impulsivity in which an individual exhibits poor behavioral control or aggression in the setting of a negative event or affectNeuromodulation: a category of brain treatments that modulate or alter neuronal activity through direct electrical or chemical stimulationTranscranial magnetic stimulation: a non-invasive brain treatment that applies a magnetic field directly to the scalp, activating neuronal activity and neuroplasticity to specific cortical regions of the brainIntermittent theta burst stimulation: a novel second-generation form of transcranial magnetic stimulation that utilizes bursts of magnetic energy known as theta bursts

### Rationale

#### SI Epidemiology and Current Treatment

SI is a severe and prevalent condition among veterans and civilians alike and can prove lethal. The Centers for Disease Control and Prevention estimates that from 2015 to 2019, 4.3% of the general adult US population had SI, and 5% to 10% of these individuals advanced to making a suicide attempt (SA) [33]. Consequently, focusing treatment on individuals with SI before they advance to making an SA gives providers an opportunity at suicide prevention.

Current evidence-based treatment options for SI include pharmacotherapy and psychotherapy. Pharmacotherapeutic treatment (primarily antidepressants) can take 6 to 8 weeks or more to become effective [34]. A recent meta-analysis suggested that only two-thirds of the published studies demonstrated a reduction in SI with any pharmacotherapy compared to placebo [35]. Furthermore, many patients will require multiple medication trials and may take months to experience any symptomatic improvement [36]. Given the latency of these treatment options, individuals with SI require more suicide prevention interventions that are designed to exhibit better and faster resolutions toward promoting resilience.

#### mTBI and Suicide: The Role of Impulsivity

Impulsivity is associated with TBI of all severities [16,37,38]. For this study, we will focus on veterans with mTBI. Veterans with mTBI make up the majority (>80%) of the veteran population with TBI in the United States [3]. A form of behavioral impulsivity, negative urgency impulsivity, is particularly prevalent in this population [38]. Negative urgency impulsivity refers to poor behavioral control in the setting of negative events or affect [39]. It is associated with excessive agitation, irritability, low moods, and a greater tendency for aggression toward oneself or others immediately following a negative event [40]. Unsurprisingly, negative urgency impulsivity increases the likelihood of SI [41] and is associated with significant risk factors for suicide, such as social and occupational functional deficits [42]. Our laboratory’s previous work built upon these findings and completed a chart review study that found negative urgency impulsivity most strongly mediated the relationship between a history of TBI and SI and SAs [43].

Post-TBI negative urgency impulsivity is presumed to be secondary to disinhibition of the limbic system from TBI-related damage to the prefrontal cortex, specifically the VMPFC, medial orbitofrontal cortex, or both [16]. The VMPFC, which serves as an inhibitory control center for the limbic system, is particularly vulnerable to damage in all severities of TBI as this region abuts the cranial floor and frontal cranial bone, making it susceptible to coup and contrecoup forces from nearly all directions [31,44,45]. Uninhibited limbic effect can manifest as poor frustration tolerance, fear, and aggression [46]. These characteristics of negative urgency impulsivity can reduce the quality of life and worsen community and social functioning, predisposing individuals to SI and SAs (Figure 1) [46].

To the best of our knowledge, no neuroimaging evidence implicates specific brain regions in mTBI-related impulsivity and SI. The presented study will help address this knowledge gap using within-participant neuroimaging data to identify brain regions predisposed to these conditions.

**Figure 1 figure1:**
[figure not shown]
Relationship between impulsivity, functionality outcomes, and suicidal ideation.

#### mTBI and Suicide: The Role of Functional Deficits

TBI itself predisposes individuals to social and occupational functional deficits [47]. A meta-analysis of psychosocial factors found that difficulties in social and occupational functioning were strongly tied to increased levels of SI, social isolation, and low socioeconomic status and are directly associated with increased incidences of SI and completed suicides (Figure 1) [48]. Among individuals with TBI, those who were unemployed in the past year were at the highest risk for SI when compared to individuals who had been employed [17]. Given that TBI and impulsivity are both (1) independent risk factors for developing SI and (2) associated with impaired social and community functioning, it appears that TBI, SI, impulsivity, and functional deficits are intertwined and should be considered in tandem. However, the evidence is scarce to directly support biological treatments for SI, impulsivity, and functional deficits following mTBI. This study aims to address this knowledge gap by providing further evidence to support the development of a novel neuromodulatory treatment to improve functioning for those with impulsivity, SI, and mTBI symptoms.

#### TMS in Neuropsychiatry

TMS is a noninvasive neuromodulatory technique that involves placing an insulated electric coil on the scalp [49]. The electrical current flowing through the coil produces alternating magnetic fields. These fields pass through the skull, inducing electric currents in the brain tissue beneath the coil [50]. In large, multisite, double-blinded, sham-controlled trials, TMS applied [51,52] to the left dorsolateral prefrontal cortex (DLPFC) was shown to effectively treat depression. TMS was subsequently approved by the FDA to treat treatment-resistant depression in 2008 [53-55]. In 2020, a nationwide clinical TMS program was implemented in the US VA after completing a multisite clinical trial. Thus, the VA health care system is well-positioned to offer novel TMS treatment approaches for veterans in need.

iTBS is a second-generation FDA-approved form of TMS designed to mimic endogenous brain rhythms with the added benefit of markedly reduced treatment time [28,56]. In iTBS, 50 Hz triplets are applied at a theta rhythm (5 Hz), which is thought to facilitate long-term potentiation in less time and with fewer pulses than standard TMS, which generally is administered at 5 to 10 Hz [57]. Using this approach, iTBS can be administered in 3 to 10 minutes, compared to the standard 37.5-minute protocol for first-generation TMS [58]. One of the most prevalent and widely known iTBS treatment protocols is based on a study by Li et al [58] and delivers 1800 pulses of iTBS per day for 10 days. This amount of stimulation appears to be well tolerated and shows a good effect on depressive symptoms, even in a treatment-refractory group [58]. Studies demonstrate that this number of pulses results in an optimal “window” of cortical excitability, and additional pulses may have an inhibitory effect [59-61]. The result of significant symptomatic improvement in a short period is particularly interesting and relevant in treating SI, where a shorter latency to treatment response is of the essence and could potentially be lifesaving.

#### TMS as a Treatment for TBI Sequelae

TMS has an established safety record as a treatment for individuals with mTBI [23]. There is accumulating evidence supporting the safety and efficacy of TMS for sequelae of mTBI and related neuropsychiatric conditions, including depression, cognitive deficits, and chronic pain or headaches [23-26]. TMS also improves PTSD symptoms among those with co-occurring mTBI [22,27]. Further, multiple studies and meta-analyses demonstrate that TMS, administered to a variety of brain locations, including the DLPFC, does not induce more significant numbers of AEs among individuals with mTBI than among individuals without mTBI [23,25,62,63]. Specifically, in a national US VA TMS study of 770 veterans receiving TMS, nearly half had mTBI, and TMS was demonstrated to be equally safe in veterans with and without mTBI [64].

An overall estimate of 70% of individuals with mTBI struggle with at least one psychiatric comorbidity [65]. Thus, it is essential to consider TBI and comorbid mental illness simultaneously, as they frequently co-occur. Comorbid conditions include substance use disorders, PTSD, and depression [66-68]. Moreover, neuroimaging studies of individuals diagnosed with PTSD and substance use disorder (2 conditions that are also associated with impulsive behavior and SI) demonstrate diminished volume and hypoactivity in the VMPFC [69,70]. Therefore, it is likely that when mental illness diagnoses such as PTSD and substance use disorders co-occur with mTBI, they have an additive effect on brain functioning in the VMPFC, further worsening negative urgency impulsivity [69,70].

#### TMS as Treatment for Suicidality

Encouraging meta-analyses suggest that TMS may also effectively treat suicidality [71,72]. For example, a randomized controlled trial (RCT) reported a 44% decrease in individuals experiencing “thoughts of suicide” after high-dose left-sided DLPFC TMS treatment [73]. In addition, a study of pooled sham-controlled trials reported that bilateral TMS is associated with a decline in SI [74].

However, drawing overall conclusions from the existing literature on TMS for suicidality remains challenging because of the heterogeneity of the data. Studies are often limited by small sample sizes, inconsistencies in how suicidality is measured across studies, and contradictory findings [75,76]. Interestingly, an analysis suggests that changes in SI may be statistically independent of depression outcomes, underscoring the importance of studying SI separately from depression in contrast to many previous studies [77].

Post-TBI negative urgency impulsivity is presumed to arise from limbic system disinhibition because of damage to the VMPFC [16]. In mTBI, thinning of the right VMPFC is evident when compared to healthy controls [78]. Individuals exhibiting this volume loss report increased aggression, anxiety, and depression following injury [79]. Uninhibited limbic effect can manifest as poor frustration tolerance and aggression, characteristics of negative urgency impulsivity [80]. Interestingly, individuals without a history of mTBI who attempted suicide or have a history of SI also show diminished VMPFC volume and reduced connectivity between the prefrontal cortex and the limbic system, further supporting it as a potential therapeutic target [31,81]. Our study will collect MRI data to support our hypothesis that iTBS increases neuroconnectivity between the VMPFC and limbic system.

Frontal pole stimulation is a recent TMS and iTBS site of interest for reducing impulsive behaviors, including substance abuse [82] and compulsions in obsessive compulsive disorder [83]. iTBS can be applied to the frontal pole to target the VMPFC, and iTBS to the frontal pole is tolerable, with no more subjective pain than TMS [63]. This approach allows for more direct stimulation of the VMPFC and modulation of the limbic system [63,82].

This study proposes inducing neuroplasticity to the VMPFC by stimulating the frontal pole to treat SI and impulsivity in veterans with mTBI. We selected the frontal pole and associated right VMPFC as a treatment target as volumetric data demonstrates thinning of the right medial orbitofrontal cortex and VMPFC when compared to healthy controls [78]. Individuals exhibiting this volume loss also report increased aggression, anxiety, and depression following injury [79]. The role of the VMPFC in negative urgency impulsivity is also supported by evidence that individuals with penetrating TBI to the VMPFC are significantly more likely to become aggressive than those with penetrating TBI elsewhere [44]. By inducing modulation and neuroplasticity to the VMPFC and limbic system, iTBS at the frontal pole offers a promising means of mitigating impulsive behaviors and decreasing SI by increasing connectivity and undoing limbic damage caused by mTBI. However, more research is essential to ensure safety, tolerability, and efficacy of this treatment approach.

### Objectives

This pilot study aimed to (1) determine the safety, feasibility, tolerability, and efficacy of frontal pole iTBS for veterans with mTBI, negative urgency impulsivity, and SI; (2) collect advanced neuroimaging data from veterans with mTBI, impulsivity, and suicidality to further our understanding of what neural changes are occurring when treatment is effective; and (3) gather preliminary clinical outcome data on impulsivity, SI, and social and occupational functioning of veterans receiving iTBS. The results of these objectives will help to guide future studies on neuromodulation as a treatment for impulsivity and SI among patients with mTBI.

### Hypotheses

Our central hypotheses are that frontal pole iTBS will be safe, feasible, and tolerable among veterans with mTBI based on existing literature that suggests frontal pole iTBS is as safe and tolerable as iTBS performed elsewhere [23,25,62]. Similarly, iTBS, when administered to individuals with mTBI is as safe and tolerable as in individuals without mTBI [63]. Given that we are using an established iTBS protocol within the established TMS safety guidelines [84], we do not anticipate significant AEs.

We further hypothesize that social and occupational functioning, negative urgency impulsivity, and SI will be improved for individuals who receive active-iTBS compared with those who receive sham-iTBS. Even if only a single domain improves, we consider this a positive finding.

In addition, we hypothesize that resting-state functional connectivity between the VMPFC and the limbic system (especially the amygdala and anterior cingulate cortex) will be strengthened for the active-iTBS group compared with the sham-iTBS group. We also expect that veterans with increased connectivity between these regions of interest (ROIs) will likely show the most functional improvements.

Pending the results of this pilot trial, larger-scale RCTs may be warranted to establish the efficacy of frontal pole iTBS for social and occupational functional deficits, negative urgency impulsivity, and SI.

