### Power Analysis and Sample Size Justification

To ensure we have adequate power to detect a difference in our primary outcome, the Social and Occupational Functioning Assessment Scale (SOFAS), we conducted a power analysis. Assuming a significance level of 0.05, a mean SOFAS score of 44.6, and a SD of 15, with 50 veterans, we will have 82% power to detect a significant interaction between time and treatment assuming no change over time in the sham-iTBS group and a change of 13 points in the active iTBS group [90]. On the basis of similar studies of iTBS protocols for patients with depression and PTSD, receiving treatment of similar duration, attrition rates are expected to be low—under 10% [58,90,91]. As such, we plan to enroll participants to ensure we have an adequate sample size considering 10% attrition. Thus, our total sample size will be 56 with 28 in the active iTBS group and 28 in the sham iTBS group.

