**Phone screening assessments**					
	Ohio State TBI^a^ Identification Method [92] (rater administered)	mTBI^b^ eligibility determination	Structured interview	Determination of the likelihood TBI sustained based on the participant’s detail recollection	Interrater reliability >90% (very high) [92]
	Columbia Suicide Severity Rating Scale [89] (rater administered)	History of suicidality, eligibility determination—secondary outcome	Five items measuring the presence of SI^c^, intensity of SI, presence of suicidal behaviors, lethality of behaviors	Ideation: 0-5; intensity: 2-25; suicidal behaviors: yes or no; lethality: 0-2, higher scores=more severe	Internal validity a=0.95 and test-retest reliability r_*tt*_*=*0.90-1.0 (very high) [93,94]
	Urgency, Premeditation (lack of), Perseveration (lack of), Sensation Seeking, Positive Urgency Impulsive Behavior Scale—Negative Urgency subscale [41,95] (rater administered)	Negative urgency impulsivity, eligibility determination—secondary outcome	Fifty-nine items measuring 4 traits–urgency, lack of premeditation, lack of perseveration, and sensation seeking [96]	4-point Likert scale questions, scored by each trait, some reverse-coded. Higher score=more severe [97]	Cronbach α=0.91 (very high) [41,97]
	Demographics (rater administered)	Sample characterization	—^d^	—	—
	UIC^e^ CMRR^f^ MRI^g^ Safety Form (Multimedia Appendix 2; rater administered)	MRI safety, compatibility, and eligibility determination	—	—	—
	TMS^h^ Safety Form (Multimedia Appendix 4; rater administered)	TMS safety compatibility, eligibility determination	—	—	—

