### Analytic Plan

A statistical significance level corresponding to α=.05 will be used to test hypotheses.

Descriptive statistics of feasibility, safety, and tolerability measures will be computed for all participants and compared between active- and sham-iTBS groups. We will calculate the categorical variables’ frequencies and compare them using chi-square analyses for the descriptive statistics [126]. For the continuous variables (ie, daily pain ratings), we will compute mean, median, range, and SDs and compare using 2-tailed *t* tests.

For functional outcome measures, we will estimate a mixed model ANOVA to measure differences within-participants (how the SOFAS changes over time), between-participants (how the SOFAS differs between active and sham iTBS), and whether there is a significant interaction between time and treatment [127]. We will assume equal variance between test and control groups [128]. If the variance is unequal, we may transition to a generalized linear mixed (GLM) effects model [129].

For our neuroimaging analysis, to evaluate the VMPFC to the amygdala and anterior cingulate relationships and how they change before and after treatment, we will define ROIs for the amygdala and anterior cingulate with clear anatomical boundaries identified using Freesurfer [130]. Average time-series data will be extracted, and GLM will be used to quantify the relationship between the seeds and targets. The GLM results will yield individual *r* values (ie, correlations), which will be normalized into *Z* scores using Fisher R-to-Z transformation [131]. The individual maps of *Z* scores will be the primary measure of connectivity between the seed and target ROIs. We will then implement an ROI-to-ROI analysis within the connectivity toolbox to evaluate resting-state functional connectivity between the amygdala, anterior cingulate, and VMPFC [132]. We will assume a normal distribution and use Fisher’s *Z* test to compare active-iTBS and sham-iTBS groups, both before and after treatment [133]. We will adjust for a priori covariates, including age, sex, and baseline psychiatric diagnoses. All analyses will be corrected for multiple comparisons using false-discovery rate correction. We will use linear mixed models to test how connectivity changes correspond to functional and mental health outcome changes, with functional and behavioral measures included as the dependent variables [134].

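### Counting improvement in any one of three domains as a positive finding conflicts with SOFAS as the single powered primary outcome, and the scope of the false-discovery-rate sentence leaves either the error rate or the stated power wrong

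*Protocol article*

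**What the plan says.** All references are to the protocol article.

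- **Introduction, Hypotheses.** The clinical hypothesis is that "social and occupational functioning, negative urgency impulsivity, and SI will be improved for individuals who receive active-iTBS compared with those who receive sham-iTBS". The next sentence reads: "Even if only a single domain improves, we consider this a positive finding".
- **Methods, Power Analysis and Sample Size Justification.** One outcome is singled out. The aim is "adequate power to detect a difference in our primary outcome, the Social and Occupational Functioning Assessment Scale (SOFAS), we conducted a power analysis". The result is 82% power with 50 veterans at a significance level of 0.05, with 56 enrolled to allow for 10% attrition.
- **Methods, Table 1, phone screening assessments.** The Columbia scale (C-SSRS) is labelled "History of suicidality, eligibility determination—secondary outcome" and the UPPS-P subscale "Negative urgency impulsivity, eligibility determination—secondary outcome". SOFAS is marked primary further down the same table.
- **Methods, Analytic Plan, opening line.** "A statistical significance level corresponding to α=.05 will be used to test hypotheses". No split of alpha and no testing order across the three domains is given.
- **Methods, Analytic Plan, neuroimaging paragraph.** The only multiplicity statement in the article: "All analyses will be corrected for multiple comparisons using false-discovery rate correction". It follows the connectivity group comparison and its covariates, but its wording is not limited to them.

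**The concern.** Two rules compete for the same conclusion. Under the sample-size section and Table 1, the efficacy result is the SOFAS comparison. Under the Hypotheses section, any of three domains will do. Suppose SOFAS is null and UPPS-P negative urgency gives p=.04. The first rule says the primary outcome failed; the second calls the result positive.

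This matters because the Objectives and Study Design list efficacy among the things to be determined or examined, and the Hypotheses section makes larger trials depend on the results. A chance difference on one of three domains could steer that decision. The plan should say before unblinding which comparison carries the efficacy conclusion, and whether the multiplicity correction applies to it.

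**Working it through.** **Inputs from the article.** Three domains; α=.05; SOFAS change of 13 points in active and 0 in sham; SD 15; 50 evaluable veterans (25 per arm); 10% attrition; 56 enrolled.

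**Assumptions, because the article gives no figure.** Efficacy tests are two-sided. The correlation between the three test statistics is varied over a range. The within-person correlation of SOFAS is set where it reproduces the stated power.

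**1. The plan's own figures.**
- Enrolment: 50/(1−0.10) = 55.6, rounded up to 56. This agrees.
- Power: the SD of 15 is not identified as the SD of a score or of a change, and no within-person correlation ρ is given. Read as the SD of change, power is 85.1% (noncentral t) or 86.5% (normal approximation). Read as the SD of a score, the SD of change is 15·√(2(1−ρ)). At ρ=0.45 this is 15·√1.10 = 15.73, the standard error of the difference is 15.73·√(2/25) = 4.45, and the standardised effect is 13/4.45 = 2.92. Power is then 81.7% (t) or 83.2% (normal). So ρ of about 0.45 reproduces the stated 82%, and it is used below.

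**2. FDR sentence read as imaging only.** The three domains are each tested at .05 without adjustment. Under the global null with independent tests:
- at least one domain significantly favouring active: 1−0.975³ = 7.3%, against 2.5% for SOFAS alone;
- at least one significant difference in either direction: 1−0.95³ = 14.3%, against 5% for SOFAS alone.

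With equicorrelated normal statistics (2 million simulated draws):

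| Correlation | Favouring active | Either direction |
|---|---|---|
| 0 | 7.3% | 14.3% |
| 0.3 | 6.8% | 13.6% |
| 0.5 | 6.3% | 12.6% |
| 0.7 | 5.5% | 10.9% |
| 0.8 | 4.9% | 9.8% |

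The rule is about improvement, so the middle column is the relevant one.

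**3. FDR sentence read as covering the three clinical domains.** With the Benjamini-Hochberg procedure over three tests, at least one false rejection in either direction under the global null occurs in 5.0% at correlation 0, falling to 3.8% at 0.9. The error is controlled. SOFAS, however, is then compared with .05/3, .10/3 or .05 according to how the other two domains turn out. With 25 per arm, ρ=0.45, and the other two domains null and independent, SOFAS power falls from about 83% to about 71% (both on the normal approximation).

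**4. Side by side.** Reading 2 keeps the stated power and loses control of the any-domain error. Reading 3 keeps the error and loses the stated power. On neither reading do the one-of-three sentence, the flat .05 and the 82% all hold together.

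**The case against.** The strongest reply is that this is a pilot. Its central hypotheses are safety, feasibility and tolerability, its clinical data are called preliminary, and establishing efficacy is left to larger trials. The sentence stands in the Introduction and is not repeated in the Analytic Plan, and the primary and secondary labels are stated. A detailed testing hierarchy commonly belongs in an analysis plan that is not shown. This lowers the stakes, and it rules out demanding strict familywise control of every secondary signal. It does not remove the conflict: the article still powers one outcome formally, sets α for hypothesis tests, lists efficacy as an aim, and prints a rule that bypasses the powered outcome.

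A reader might infer more than the text supports:

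- *That the plan declares the whole trial positive on one domain.* It speaks of a positive finding and defines no criterion for trial success.
- *That false positives run at two to three times the stated 5%.* That multiple belongs to differences in either direction, which would count active being worse than sham. For improvement only, the rate is about 1.0 to 1.5 times 5% (4.9/5 to 7.3/5). It is two to three times only when set against the 2.5% directional error of a single test.
- *That the inflation is certain.* Read literally, the FDR sentence would remove it.
- *That the rate could reach 30%* (1−0.95⁷ = 30.2%) because Table 1 has seven scales touching these domains. The article does not say that any scale may define success in a domain, and independence among scales of one construct is implausible.

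**Conclusion.** The point holds as a conflict between stated rules, with a moderate numerical consequence. The one-of-three sentence cannot stand beside a single powered primary outcome and two outcomes labelled secondary.

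If the FDR correction is confined to imaging, which its position suggests, the chance under the global null of at least one domain significantly favouring active is about 5–7%, against 2.5% for SOFAS alone (about 10–14% against 5% in either direction). If it extends to the three clinical domains, the error is at or below 5%, but the stated 82% power does not describe the planned SOFAS test.

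The error rates rest on two-sided tests and on assumed correlations of 0.8 down to 0. The 71% rests on a within-person correlation of 0.45 and on the other two domains being null and independent; other configurations would give other values. The conflict itself needs none of these assumptions.

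**What to change.** 1. In Hypotheses, replace the one-of-three sentence with a statement that the efficacy conclusion rests on the active-versus-sham comparison of SOFAS at two-sided .05.
2. State there that negative urgency and SI are secondary, will be reported as estimates with confidence intervals, and cannot by themselves make the efficacy result positive.
3. In the Analytic Plan, limit the FDR sentence explicitly to the ROI connectivity analyses.

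The cost is wording. Enrolment stays at 56, and SOFAS keeps its full .05 and its planned power. The downside is that an isolated result on SI or impulsivity can be called only a preliminary signal, which suits a pilot.

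If the sponsor prefers to keep a one-of-three rule, it should state the adjustment and redo the power. For example, Bonferroni at .05/3 = .0167 per domain gives a familywise rate of 1−(1−.0167)³ = 4.9% at independence, but SOFAS power falls from about 82% to about 67% (noncentral t, 25 per arm, within-person correlation 0.45).

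The article reports 2 participants enrolled as of July 2024 and no outcome analysis. The change should be made and dated before any unblinded look at the data.
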